## Methods/Design

### Design

The study uses a randomized controlled two-armed design comparing a psychological counseling intervention (that is, the *verum* intervention) with an active control intervention after patient inclusion in the study. Sequence generation is done in a 1:1 fashion based on a computer-generated random list with randomly varying blocks of 20. The randomization sequence is generated by the website Research Randomizer (http://www.randomizer.org). The list is concealed by instructed office personnel in the study center of the Division of Psychosomatic Medicine, University of Bern, Switzerland, who is unaware of any patient information and localized off-site from the CCU. Study therapists receive the information to provide either the *verum* intervention or the control intervention directly from the study center.

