### Timing of assessments

Patients will be assessed at three time points: on the CCU within 48 hours after MI (T0), at three months after discharge from the CCU (to assess acute posttraumatic stress) (T1), and at 12 months after discharge from the CCU (to assess chronic and late-onset posttraumatic stress) (T2). It is critical to approach patients at the earliest possible time after referral because they will usually stay for only 48 hours in the CCU before discharge. Therefore, within 12 to 24 hours of admission to the CCU (T0), all patients with STEMI/non-STEMI, aged 18 and older, and with stable circulatory condition will be informed about the planned study and are given a few hours to consider their participation. The study therapist will approach all eligible patients to ask about their willingness to participate in a single counseling session about the role of psychological stress in CHD and the possibilities to self-manage stress. Patients will be told that the provided information might be useful for good mental functioning while building up their life after MI. The patient will be told that if he/she agrees to participate he/she will be randomized to either counseling session A, targeting the more sudden and unexpected psychological stress which may occur in the aftermath of MI (that is, the *verum* intervention) or to counseling session B, targeting more general aspects about the role of psychosocial stress in MI (that is, the control intervention). During this information, study therapists avoid any terminology specifically pertaining to trauma. After having provided informed consent, and if reporting a sufficient amount of distress from MI, they will undergo medical and psychometric data assessment as specified below.

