### Intervention

Study therapists with a master’s degree in clinical psychology deliver the intervention within 48 hours of admission, as a single session of 45 minutes with the therapist by the bedside. Therapists are trained and supervised by senior clinical psychotherapists with degrees in psychology or psychiatry from the Clinical Psychology and Psychotherapy, Department of Psychology, University of Bern and Department of Psychiatry and Psychotherapy, University Hospital Zurich, Switzerland. Study therapists undergo at least 30 hours of training prior to beginning the trial. Two independent experts will rate 30 audiotaped intervention sequences to monitor adherence of study therapists to the intervention protocol. In addition, 50 patients from each intervention group will be asked to indicate their perception as to whether they belong to the intervention group A (that is, the *verum* group) or B (that is, the control group).

Table 1 details the components and topics of the two interventions. Each intervention consists of a counseling session of 45 minutes plus delivery of a colored information booklet for patients to deepen the oral information. Text and figures of the two booklets are specific to each mode of intervention and also serve as the basis for interacting with the patient. For the first half of the session, therapists will primarily cover topics that are of most immediate concern to the individual patient. For instance, when asking about previous stressful situations (in the control intervention) and the patient mentions a difficult situation at work, the discussion will be on job stress. Other forms of stressful life circumstances will not be covered but are dealt with in the information booklet. Nevertheless, during the course of counseling, therapists are required to inform about key topics, for instance, in the *verum* intervention, that it is a normal and common experience to perceive MI as stressful.

**Table 1 T1:** Topics and questions covered by the two interventions

***Verum *****group**	**Control group**
a) What is a trauma? Why can acute MI be understood as a traumatic experience?	a) What is psychosocial stress and when can it become dangerous?
b) Why can MI have a psychological impact?	b) Why do not all people react the same way to psychosocial stress?
c) How do patients cope with and adjust to their MI experience?	c) Which types of psychosocial stress are known to potentially have an influence on CHD and cardiac prognosis?

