### Measures

Table 2 shows all health outcomes in the MI-SPRINT study with the timing of their assessment. All psychometric questionnaires used in the MI-SPRINT study are validated in the German language [48-77]. We will apply the Clinician-Administered PTSD Scale (CAPS) to assess our primary outcome (that is, interviewer-rated posttraumatic stress level at three months after the intervention) [48]. Assessors will be blinded to the type of intervention and asked to indicate their guess as to whether the patient had received the *verum* intervention or the control intervention. The German version of the CAPS shows good internal consistency for the severity score of all 17 PTSD symptom items (Cronbach’s α = 0*.*88 to 0.92) as defined by the *DSMcpIV*[49]. The frequency and intensity of each symptom are rated between 0 (never) and 4 (almost always). A symptom is given when frequency is at least one point and intensity is at least two points. One of five symptoms is required for criterion B (reexperiencing cluster), three of seven symptoms for criterion C (avoidance cluster), and two of five symptoms for criterion D (hyperarousal cluster). The severity of PTSD is obtained by adding up symptom scores of criteria B+C+D. Patients will be diagnosed with syndromal PTSD if meeting criteria B+C+D [1].

**Table 2 T2:** Measures at hospital referral (T0), three-month (T1) and twelve-month (T2) follow-up

**Variables**	**T0**	**T1**	**T2**
Sociodemographic and medical variables			
Demographics: for example, gender age, marital status	x		
Medical history: for example, family history of coronary artery disease, diabetes mellitus, hypertension	x		
Lifestyle and health behavior: smoking history, alcohol consumption, physical exercise, sleep quality	x	x	x
Prescribed medication before CCU referral	x		
Medication administered during CCU stay	x		
Medication at discharge from CCU	x		
Context of hospital referral: for example, patient agitation state at arrival on CCU, hectic conditions on CCU at patient arrival	x		
Clinical presentation at time of arrival at CCU: for example, total number of stents implanted, number of diseased coronary vessels, left ventricular function, Killip classification, pain onset	x		
Psychometric data			
Clinician-administered PTSD Scale (CAPS) [48,49]		x	x
Posttraumatic Diagnostic Scale (PDS) [50,51]	x	x	x
PTSD screening with three items from the structured clinical interview for DSM-PTSD [52,53]	x		
Acute Stress Disorder Scale (ASDS) [54,55]	x		

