### Statistical analyses

Data will be analyzed using the latest version of the Statistical Package for the Social Sciences (SPSS Inc. Chicago, IL, USA) with a significance level of *P* < 0.05 (two-tailed). Before analysis, all outcome variables will be tested for normality by the Kolmogorov-Smirnov test and, if necessary, transformed to obtain a normal distribution. Differences in variables between the two intervention groups will be calculated using the *t*-test for continuous data and the chi-squared test for categorical data. The primary outcome is the severity of posttraumatic stress levels rated by the CAPS interview at the three-month follow-up. Secondary outcomes are measures of psychosocial functioning and cardiometabolic biomarkers at three months follow-up (primary analysis). Key secondary outcomes are quality of life, plasma levels of C-reactive protein, D-dimer, cortisol and norepinephrine, as well as high-frequency heart rate variability. These outcomes are important indicators of mental health functioning, low-grade inflammation and coagulation activity as well as hypothalamic-pituitary adrenal axis and autonomic nervous system function. Repeated measures analysis of variance will be applied to test for a change in posttraumatic stress levels and in measures of psychosocial functioning and cardiometabolic biomarkers between the two follow-up visits (secondary analysis). The relative risk for developing a diagnosis of PTSD during follow-up in the control group compared to the *verum* group will be calculated by means of logistic regression analysis. For a complementary sensitivity analysis, we will apply univariate, multivariate and repeated measures analysis of covariance taking into account sociodemographic, medical and psychosocial covariates, and received psychotherapy during follow-up.

Missing values for questionnaire items will be replaced using the expectation maximization algorithm [80]. If patients drop out during follow-up, we will carry forward the last observed data points to impute missing endpoints. Randomized patients who will not undergo the intervention are excluded from the analysis. However, we will perform an additional analysis based on the intention-to-treat principle with all randomized patients.

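### The main analysis drops randomised patients who did not have the session and makes intention-to-treat an extra, so randomisation does not protect the primary comparison

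*Protocol article*

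**What the plan says.** The rule is in the last paragraph of Statistical analyses in the protocol article: "Randomized patients who will not undergo the intervention are excluded from the analysis". The next sentence reads: "However, we will perform an additional analysis based on the intention-to-treat principle with all randomized patients". No other section makes the all-randomised set primary or limits the exclusion to reasons unrelated to the arm.

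Four other places bear on it.

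- **Design**, on who knows the allocation: "Study therapists receive the information to provide either the *verum* intervention or the control intervention directly from the study center".
- **Timing of assessments**, on what patients hear at consent: "he/she will be randomized to either counseling session A, targeting the more sudden and unexpected psychological stress", or session B on more general stress. The same section says that trauma terms are avoided at that stage. It also explains the short time available, since "they will usually stay for only 48 hours in the CCU before discharge".
- **Measures**, on outcome rating: "Assessors will be blinded to the type of intervention".
- **Table 2**: CAPS, the primary instrument, is scheduled at three and twelve months only, not at T0. Statistical analyses fills missing endpoints of dropouts by carrying the last observation forward.

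**The concern.** Randomisation makes the two arms comparable as allocated. Once membership of the analysis set depends on something that happens later, that guarantee covers only those aspects of the later event that are unrelated to the arm.

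Excluding untreated patients can be harmless when nobody who influences receipt can know the allocation. That safeguard is absent here. The study therapists approach patients about taking part, are told which session to give, and deliver it at the bedside in a short stay. The sessions differ in subject: one deals with the infarction as a trauma, and the other avoids that topic. A session could therefore be less likely to take place for a certain kind of patient in one arm than in the other. If those patients also differ in their expected month-3 score, the main comparison is shifted, and the test of the main hypothesis no longer has its stated error rate.

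**Working it through.** **1. The plan's own figure.** The Sample size calculation gives a difference of 2.9 PDS points, SD 10.1, alpha 0.05 and power 80%; Statistical analyses makes the test two-tailed.

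n per group = 2 × (1.960 + 0.842)² × 10.1² / 2.9² = 190.4, so 191 (192 with the t distribution). The plan states 194, and 194 × 1.10 = 213.4 matches its 213 per group. The sample size is not in dispute.

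**2. Size of a possible shift.** The documents give no rate of missed sessions and no prognosis for those patients, so f and D below are assumptions. The scale is PDS because the plan states its target effect only on that scale.

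Let a fraction f of the verum arm be excluded, with a mean D points above the remaining verum patients, and let nobody be excluded from control. The whole-arm mean is (1 − f) × m + f × (m + D) = m + fD. Exclusion therefore lowers the verum mean by **f × D**.

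Under no true effect, with 213(1 − f) against 213 patients, the standard error is 10.1 × √(1/[213(1 − f)] + 1/213), which is 0.98, 0.99 and 1.01 for f = 2%, 5% and 10%. The two-sided error at nominal 0.05 is Φ(−1.96 + fD/SE) + Φ(−1.96 − fD/SE).

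| f (verum only) | D | Shift fD | Share of 2.9 | Type I error |
|---|---|---|---|---|
| 0%, or equally selective in both arms | any | about 0 | about 0% | about 5% |
| 2% | 5 | 0.10 | 3% | 5.1% |
| 2% | 10.1 (1 SD) | 0.20 | 7% | 5.5% |
| 5% | 5 | 0.25 | 9% | 5.7% |
| 5% | 10.1 | 0.51 | 17% | 8.0% |
| 10% | 5 | 0.50 | 17% | 7.9% |
| 10% | 10.1 | 1.01 | 35% | 17.1% |

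If the excluded verum patients scored lower than the rest, or if the selective exclusion were in the control arm, the sign would reverse.

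**3. Cost of making the all-randomised set primary.** Suppose a fraction f of verum patients miss the session and score like control patients. The difference becomes 2.9 × (1 − f). With all 213 per group assessed, SE = 10.1 × √(2/213) = 0.979, and power = Φ(difference/0.979 − 1.96).

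| f | Difference | Power, 213 per group |
|---|---|---|
| 0% | 2.90 | 84.2% |
| 2% | 2.84 | 82.7% |
| 5% | 2.76 | 80.4% |
| 10% | 2.61 | 76.0% |

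With only 194 per group analysed, power is 76.6% at f = 5% and 72.1% at f = 10%.

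A harsher case uses the plan's expected score of 15.2 for high-risk patients without the assumed benefit of either session. Verum patients who miss the session then score 15.2, and the difference is 14.2 − [11.3(1 − f) + 15.2f] = 2.9 − 3.9f. That is 2.705 at 5% and 2.51 at 10%, giving 78.9% and 72.7% power with 213 per group.

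**4. Whether the additional analysis works as written.** A randomised patient without a month-3 interview has no earlier CAPS score, because Table 2 has none at T0. The carry-forward rule has nothing on the primary scale to bring to month 3.

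**The case against.** The strongest reply is that the trial has several protections. Assessors are blinded, both arms receive a 45-minute session, patients have agreed in advance to either one, and an all-randomised analysis is prespecified, so a divergence between the two results would be visible. Many missed sessions could also have causes unrelated to the arm, such as early transfer or discharge. This stands as far as it goes: it makes a large bias less likely. It does not make the main comparison a randomised one, and blinded rating has no bearing on who is excluded.

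A reader might go further and infer three things that the documents do not support.

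- **That the bias favours verum.** Avoidance is a PTSD symptom cluster, so it is tempting to suppose that the worst-affected patients would escape the trauma session. The article gives no rate, reasons or prognosis of non-receipt by arm. Its Background describes PTSD symptoms as lasting at least a month, while the session takes place within 48 hours.
- **That patients would refuse a trauma-focused session.** Consent information avoids trauma terms, and no section says that patients learn their arm before the session begins. The perception check ("50 patients from each intervention group will be asked to indicate their perception as to whether they belong to the intervention group A") shows that recognising the arm is thought possible, not that it precedes the session. The therapist's knowledge is the firmer route.
- **That sessions broken off part-way are excluded.** The rule concerns patients who do not undergo the intervention; it does not say how an incomplete session counts.

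**Conclusion.** The point holds. The main analysis set is defined by an event after randomisation, staff who know the arm are placed to influence that event, and the all-randomised analysis has only a supporting role. This is a stated rule, not detail left to a fuller document.

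What is certain is the loss of protection, not the amount of bias. The shift is near zero if non-receipt is rare or equally selective. It reaches about 0.1 to 1.0 PDS points (3% to 35% of the target difference) only on the assumption of verum-only non-receipt of 2–10% in patients 5–10 points worse than the remaining verum patients. The documents do not establish a direction.

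**What to change.** - Make the primary analysis all randomised patients in their allocated arm, and the session-received analysis secondary.
- State that CAPS is sought at three and twelve months whether or not the session took place.
- Report the number of sessions not received, with reasons, by arm, and say how an incomplete session is classified.
- Replace last observation carried forward for missing month-3 CAPS with a method that can work without a baseline CAPS. One option is multiple imputation using measures that Table 2 schedules at T0, such as the PDS and the Acute Stress Disorder Scale.

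The cost is two sentences exchanged, one imputation rule rewritten, and follow-up interviews for patients who missed the session. The planned 213 per group can stay. The downside is some dilution: about 80% power at 5% verum non-receipt and 76% at 10%, if those patients fare like controls and all 213 per group are assessed. Power is lower if month-3 interviews are missing.

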## Discussion

The MI-SPRINT study is a randomized-controlled trial to investigate whether a minimal psychological intervention applied shortly after hospital referral may reduce the probability of developing clinician-rated posttraumatic stress levels attributable to MI. If effective, the planned trial will be the first to show that the development of posttraumatic stress can successfully be reduced in MI patients at high risk to develop PTSD through a single 45-minute counseling session that is feasibly (for example, not excessively time-consuming) administered in a busy CCU setting.

Cardiac patients with high risk to develop PTSD have generally limited access to early psychological care. Therefore it is important to know whether such an intervention bears the potential to become an integrative part of the post-acute treatment phase of patients with acute MI to improve quality of life and perhaps cardiovascular prognosis as well. Regarding the latter, a relative improvement of the atherothrombotic risk profile in the *verum* group might stimulate a larger intervention trial to possibly improve cardiac prognosis in patients with high distress after MI, as biologically plausible atherothrombotic mechanisms would seem to be responsive to an early psychological intervention.

There are limitations to the study design. Firstly, only those patients who are willing to participate in the study and to fill in questionnaires will be screened; therefore, it is possible that some severely distressed patients escape the screening, as they may feel too overwhelmed by the actual events for participating. Secondly, for feasibility reasons, we did not include non-German speaking patients, who constitute a significant part of the Swiss population. Therefore, the generalizability of our study findings to non-German speaking residents might be questioned. Nonetheless, the prevalence rates of PTSD in ACS patients do not vary greatly by study location (United States versus elsewhere, including Europe) [7]. Thirdly, although the control intervention avoids trauma terminology, an indirectly beneficial effect cannot fully be excluded, for instance if patients in the control group learn to better cope with general psychological distress. In this case, however, a group difference in posttraumatic stress levels that remains significant would only substantiate an assumed benefit of the trauma-focused *verum* intervention.

Several considerations on the design of the MI-SPRINT trial will need to be taken into account for the interpretation of study findings. We will assess posttraumatic stress at three-month follow-up, although ACS-induced PTSD symptoms at one-month might show greater variability and have been associated with recurrent CVD events [22]. Although we plan an exploratory analysis to investigate whether the intervention might offset recurrent CVD events, larger trials with adequate power would be needed for a reliable evaluation of this outcome. For both ethical and methodological reasons, we excluded patients with probably severe clinical depression who should receive standard antidepressant treatment, an imperative which would greatly complicate the protocol. A formal assessment of severe depression with a psychiatric interview is not feasible in this acute setting. A usual care control group might yield greater effects for the *verum* intervention, but such a design could not refute an interpretation that the mere contact with the study therapist was effective. We assess the subjective perception of the environment of acute medical care but for logistic reasons are unable to collect objective data on crowding or acuity of adjacent patients during participants’ CCU stay.

The MI-SPRINT study has several strengths; foremost its external validity, since MI patients are consecutively recruited from the cardiology department of a tertiary center with a wide rural and urban catchment area. In addition, the assessed psychometric and biomedical outcome variables and covariates are both well-established and cutting-edge measures in behavioral cardiology studies. To this extent, they may provide us with important novel insight into the prevention of posttraumatic stress development after MI and its link with psychosocial functioning and cardiometabolic risk, while also allowing us to identify potential moderating and/or confounding factors of these relationships. Finally, the MI-SPRINT study might extend our knowledge about the benefits and limits of psychological treatments for MI patients with a potential to reduce the burden on the health care system.

### Trial status

Recruitment of participants is ongoing; it began in January 2013 and is expected to end in December 2014. The final follow-up investigation is scheduled for December 2015.

## Abbreviations

ACS: acute coronary syndrome; CAPS: Clinician-Administered PTSD Scale; CCU: coronary care unit; CHD: coronary heart disease; CVD: cardiovascular disease; DSM-IV: *Diagnostic and Statistical Manual of Mental Disorders,* fourth edition; EDTA: ethylene-diamine-tetraacetic acid; HPLC: high-performance liquid chromatography; MI: myocardial infarction; MI-SPRINT: Myocardial Infarction - Stress PRevention INTervention; PDS: Posttraumatic Diagnostic Scale; PTSD: posttraumatic stress disorder; STEMI: ST-segment Elevation Myocardial Infarction.
